## **Trial Protocol and Statistical Analysis Plan**

### **1. Study design**

This is a two-center, prospective, controlled, randomized trial conducted in patients with moderate to severe DED. The flow chart is shown in Figure 1. We have developed the design and protocol based on the guidance for the Standard Protocol Items: Recommendations for Interventional Trials (SPIRIT) and the Standards for Reporting Interventions in Clinical Trials of Acupuncture (STRICTA).

### **2. Study setting and recruitment**

The study will commence on September 1, 2018, and will be completed by December 31, 2020, at the Guang'anmen Hospital, China Academy of Chinese Medical Sciences and the South Area of Guang'anmen Hospital, China Academy of Chinese Medical Sciences. DED is diagnosed according to the criteria of International DEWS by an experienced ophthalmologist. The participants identified as eligible will be randomized into two groups—acupuncture and medicine—at a ratio of 1:1. The flowchart of the trial is shown in Figure 1. The total study period for this trial is 32 weeks (Figure 2), including 8-week treatment period and 24-week follow-up period.

### **3. Inclusion criteria**

The inclusion criteria will be as follows.

(1) Individuals will be more than 18 years of age and less than 60 years of age.

(2) Participants will meet the diagnostic criteria of DED. They were required to have one or more symptoms of DED (e.g. eye dryness, foreign body sensation, itching, burning, stinging, visual fatigue, photophobia or blurred vision ) with severity of  $\geq 4$  (range: 0–10) measured by numerical rating scale (NRS). a Schirmer-I test (SIT) (with the application of cocaine, a local anesthetic) value  $< 10\text{mm}/5\text{minutes}$ , a tear film break-up time (TBUT)  $< 10$  seconds, and corneal fluorescein staining (CFS) scale  $\geq 1$ .

(3) Only the single eye with more severe scores or symptoms will be selected to observe the outcome.

(4) Participants who can complete the study, treatment, and assessments will be selected.

#### **4. Exclusion criteria**

The exclusion criteria will be as follows:

(1) participants with other ocular diseases (e.g., lacrimal duct obstruction, other conjunctiva and keratopathy) or immune system diseases (e.g., Sjogren syndrome and rheumatoid arthritis);

(2) participants with a history of surgery for DED within 3 months;

(3) participants with cardiovascular, kidney, liver, or hematopoietic system diseases, mental health disorders, cancer or other severe diseases for whom acupuncture may be inappropriate or unsafe;

(4) participants who received acupuncture within the past week;

(5) women who are pregnant or lactating;

(6) individuals who are participating in other clinical trials; and

(7) participants with a pacemaker, metal allergy, or severe fear of needles.

#### **5. Randomization and blinding**

The randomization will be performed by the Drug Clinical Trial Office affiliated with Guang'anmen Hospital using a centralized computer system. Patients were randomly assigned to the acupuncture or AT group using a block size of 4 stratified by centers, the final group assignments were placed in 120 opaque sealed envelopes, which were serially numbered and kept by a researcher not involved in treatment procedures or data analysis. After informed consent was obtained, the researcher opened the envelope according to the order in which the participant entered the trial and was provided for the prescribed treatment. All participants received either acupuncture or ATs 3 times per week over the 8-week period, and both groups were followed up for another 24 weeks.

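### A fixed block of 4 by centre, with visible treatments, would let a recruiter who tracks assignments know about a third in advance, and the envelope series per centre is not specified

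*Combined protocol and SAP*

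**What the plan says.** All references are to the combined protocol and SAP.

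- **Design.** Section 1: "This is a two-center, prospective, controlled, randomized trial". Section 2 sets allocation "at a ratio of 1:1" and makes eligibility a condition for randomization.
- **Sequence.** Section 5 has the hospital's Drug Clinical Trial Office randomize "using a centralized computer system", and states: "Patients were randomly assigned to the acupuncture or AT group using a block size of 4 stratified by centers". One block size is given. Nothing is said about varying it or withholding it from recruiting staff.
- **Delivery.** Section 5 describes "120 opaque sealed envelopes, which were serially numbered and kept by a researcher not involved in treatment procedures or data analysis". After consent, "the researcher opened the envelope according to the order in which the participant entered the trial". No numbering or set of envelopes per centre is described.
- **Who knows what.** The arms are acupuncture and artificial tears, and no sham or masking of participants or practitioners is described. Section 7 keeps the staff who assess the scales unaware of allocation. It also gives all investigators training that covers the protocol. Section 6 has the investigator complete the eye-examination forms and does not mention masking there.
- **Timing.** The Figure 2 schedule puts the eligibility screen at week -1. Allocation and the baseline SIT, NRS, OSDI, TBUT and CFS are all at week 0, with no order given within that column.

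**The concern.** With one known block size and visible treatments, past assignments at a centre reveal some future ones. Once either arm has been used twice in a block of 4, the rest of that block is determined. Opaque sealed envelopes prevent reading an assignment early; they do not prevent deducing it. A recruiter who knows or can guess the next arm can influence who is approached and when, so the groups may differ at entry in ways that were not randomized. Section 9 plans only unadjusted two-group comparisons, which would not address such a difference.

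Two gaps add to this. If the envelopes were one series across both centres, blocks would straddle the centres and the balance promised within each would not be secured. And because the week-0 readings have no stated order relative to allocation, nothing requires them to be recorded before the arm is revealed.

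**Working it through.** **Inputs from the documents.** Two centres (section 1); 1:1 allocation (section 2); fixed block of 4 by centre and 120 envelopes (section 5). The 120 is the only sample figure given, with no calculation behind it, so there is no plan figure to reproduce. It fits the design: 120/4 = 30 complete blocks, 60 per arm.

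**Assumptions.** The recruiter knows the block size and every earlier assignment at the centre. Complete blocks are used. The documents give no centre shares, so step 3 uses a range.

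**Step 1: assignments known with certainty (separate sequence per centre).** A 1:1 block of 4 has six equally likely orders. In two of them (AABB, BBAA) the third and fourth assignments are forced; in the other four only the fourth is.
- Forced per block: (2×2 + 4×1)/6 = 1.333
- Share: 1.333/4 = 33.3%
- Over 30 blocks: 30 × 1.333 = 40 of 120

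**Step 2: correct guesses.** Guess the arm that is behind in the block; toss a coin when level.
- Position 1: 1/2
- Position 2: 2/3
- Position 3: 1/3 × 1 + 2/3 × 1/2 = 2/3
- Position 4: 1
- Sum 2.833 of 4 = 70.8%, or 30 × 2.833 = 85 of 120, against 60 by chance

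**Step 3: the alternative reading, one series in overall entry order.** Let a share *p* of participants come from one centre, independently of list position. With 60 assignments per arm, that centre's arm difference is the difference of two Binomial(60, *p*) counts, with SD = √(120·*p*·(1−*p*)).
- *p* = 0.50: SD = √30 = 5.48
- *p* = 0.33: SD = √26.7 = 5.16
- *p* = 0.70: SD = √25.2 = 5.02

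Simulation gave a within-centre imbalance above 2 in 64-65% of trials at 50%, 62.5% at 33% and 61.5% at 70%. The 95th percentile was 11 at 50% and 10 at the other two. Mean absolute imbalance was about 4.3 (50%) or 4.0 (70%). Blocks of 4 applied truly within centre gave a mean of about 0.7 and a maximum of 2.

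Predictability falls under this reading for someone who sees only one centre. A forced assignment is recognisable only if the two earlier same-arm assignments in the block were at that centre too. Averaged over both centres, the share is (*p*³ + (1−*p*)³)/3:
- *p* = 0.50: 0.25/3 = 8.3%
- *p* = 0.70: 0.37/3 = 12.3% (simulated 12.1%)

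**Step 4: effect of the remedy.** A larger fixed block of size 2*m* has forced share 1/(*m*+1). A fixed, known block of 6 would therefore still give 1/4 = 25%. Mixing sizes does more. With 4 and 6 equally likely, 60 participants per centre assumed, and a recruiter who knows the two sizes but not their order, simulation gave 5.6% certain. Guessing the arm behind gives 2.833 correct per block of 4 and 4.1 per block of 6: (2.833 + 4.1)/10 = 69.3%, or about 83 of 120.

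**The case against.** The case on the other side is substantial.

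- **Opportunity is not bias.** The 33% requires a recruiter who knows the block size and tracks every assignment at the centre. A reader might infer that selection bias occurred, or that no analysis could deal with it. The documents support neither; they show only that both conditions could be met. This limit stands.
- **Stratification is expressly stated.** A reader might infer from "the final group assignments were placed in 120 opaque sealed envelopes, which were serially numbered" that one list ran across both centres and broke the stratification. The section never says so, and separate sequences fit its reference to centres. The step 3 imbalance figures describe an unstated design with assumed centre shares. What remains is an ambiguity to be cleared up.
- **The two problems are alternatives.** They cannot both apply at full size: under a pooled series, single-centre predictability drops to about 8-12%.
- **Consent is not the only gate.** A reader of section 5 alone might think so. Section 2 also requires eligibility, the section 3 criteria require symptom and eye-test values, and screening is at week -1.
- **Study eye.** A reader might infer that the eye is chosen at week 0, alongside allocation. The schedule has no row for this choice; the rule appears only among the inclusion criteria. Only its recording time is unspecified.
- **Safeguards exist.** Central generation, opaque envelopes, a custodian outside treatment and analysis, and masked scale assessors all help. But none prevents deduction from a known block, and the custodian is not said to be outside screening or enrolment.
- **The remedy barely changes guessing.** Correct; the gain is in certain assignments only.

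**Conclusion.** The point holds as a cheap improvement. If envelopes are used in sequence within each centre, an expected one third of assignments (40 of 120) could be known beforehand and 71% guessed correctly. Those figures are exact for a fixed block of 4 at 1:1, given an observer who knows the block size and the centre's past assignments. The plan makes both available: the block size is in the protocol on which investigators are trained, and the treatments are visible.

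The missing description of envelope series per centre is a secondary ambiguity. Only if one series were opened in overall entry order would the stated stratification fail. On assumed centre shares, imbalance within a centre would then exceed 2 in about 62-65% of trials. The unstated order of allocation and week-0 measurements is a further gap of the same kind. The documents do not show that selection took place, that a pooled list was used, or that the eye was chosen after allocation.

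**What to change.** Amend section 5 to state that:

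1. Each centre has its own randomization list, with assignments released by the Drug Clinical Trial Office's central system or, if envelopes are kept, from a separately numbered series per centre.
2. Block sizes vary at random, for example between 4 and 6. The sizes are kept out of the protocol text and training seen by recruiting staff.
3. Whoever holds and opens the assignments takes no part in screening, enrolment or assessment, in addition to the exclusions already stated.
4. An assignment is released only after eligibility, all week-0 measurements and the study eye have been recorded.

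If envelopes have already been used, the sponsor should state how they were numbered and opened at each centre, who opened them, and whether baseline values and the study eye were recorded first.

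The cost is a regenerated list and one amended paragraph; central generation is already in place. The maximum within-centre imbalance rises from 2 to 3 (half the largest block). In return, certain assignments fall from 33% to about 6%. Best-guess accuracy falls only from 71% to about 69%, so the change should not be presented as removing predictability altogether.

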#### **6. Data collection**

The data collection will be from the case report forms recorded by the investigator in the trial. The demographic, clinical, and examination results of DED from the

participants will be recorded at baseline and during the treatment and follow-up periods. Moderate to severe DED will be diagnosed by an experienced ophthalmologist after an ophthalmology examination. The investigator will enter all of the collected data into the case report forms. During the treatment period (8th week) and the follow-up period (32nd week), the forms concerning the questionnaire survey will be completed by the participants under the guidance of a full-time staff member; other forms concerning the ophthalmology examination will be filled in by the investigator according to objective examination results.

## **7. Quality control**

The acupuncture practitioners responsible for the acupuncture treatments must have a minimum of 5 years of clinical experience. All of the investigators will take a one-day training course for this trial. This training course will cover the study protocol, acupuncture operation, precautions for drug use, the recording method for CRF, disposal of bleeding, a researcher duties and research monitoring. Full-time researchers who are not aware of the random allocation of groups will be responsible for the assessments of all scales. During the trial, supervisors will check on case reports and acupuncture treatments once a month. Drop-outs, withdrawals (with the reasons), and the compliance of all participants will be recorded in detail throughout the treatment and follow-up period. Two postgraduates (not involved in the trial) will input the data independently and verify the database together.

## **8. Ethics and dissemination**

The study protocol was in accordance with the principles of the Declaration of Helsinki, was approved by the Ethics Committee of Guang'anmen Hospital of China Academy of Chinese Medical Sciences (approval number 2018-012-KY-01) on April 19, 2018 and was registered on April 23, 2018, at <http://www.chictr.org.cn/> (ref. ChiCTR1800015831). All important protocol modifications will be submitted to the Ethics Committee of Guang'anmen Hospital. The researchers will inform all participants of the potential risks and benefits of the study. Informed consent will be

obtained for all participants from either the participant or the participant's legal representative. All participants will be required to be able to understand written instructions, complete the examination and assessment forms. The personal information of all participants will be hidden from other users and stored in a specific cabinet with a lock. Statistics and monitoring managers will have the right to obtain the final study data set. To prevent the participants from suffering harm from trial participation, we will provide corresponding treatment and medical consultations with the ophthalmologist for free. We will disseminate the results of this study in meetings or publications when the trial is completed.

## **9. Statistical analysis**

SPSS Version 26.0 (International Business Machines Corporation, China) software will be used to perform the statistical analysis. Two-sided tests will be used for all statistical analyses. The level of significance is established at 0.05. Efficiency and safety analyses will be based on all participants at randomization according to the intention-to-treat (ITT) principle. All participants who have accepted randomization will be included in the statistical analysis of data. All original data collected from participants in the trial will be included in the full statistical analysis set. The data cannot be changed or eliminated at random. The missing data in the case report forms will be replaced by using the last observation carried forward method.We will do sensitivity analyses in the per protocol set, which included all randomised patients who had no major protocol deviation.

We will use the mean and standard deviation (SD) to describe continuous data if the data have a normal distribution and the mean and 95% confidence interval (CI) to describe continuous data if the data are skewed. We will use the percentage or 95% CI to describe categorical data. For comparisons with baseline data, we will use a paired *t*-test for continuous data and a nonparametric test for categorical data. For comparisons of the differences between the two groups, T-tests or Mann–Whitney U tests will be used for comparisons between continuous variables, and chi-square tests or Fisher's exact tests will be used for comparisons between categorical variables, as appropriate.

For assessing safety in the trial, the investigator will present the AEs and adverse reactions with tables, which will comprise the categories of AEs, the severity of AEs, the incidence of AEs, and correlation with the treatment. Every participant with serious AEs will stop receiving the intervention. All details will be reported in a timely manner.

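### Safety is placed on the intention-to-treat population, so adverse-event rates will be diluted or misattributed if anyone goes untreated or receives the other treatment

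*Combined protocol and SAP*

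**What the plan says.** The first paragraph of section 9 (Statistical analysis) names one population for both purposes: "Efficiency and safety analyses will be based on all participants at randomization according to the intention-to-treat (ITT) principle". The next sentence sets no exposure condition: "All participants who have accepted randomization will be included in the statistical analysis of data".

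The only other analysis set is per-protocol: "We will do sensitivity analyses in the per protocol set, which included all randomised patients who had no major protocol deviation". A major deviation is not defined.

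The third paragraph of section 9 describes the AE tables, "which will comprise the categories of AEs, the severity of AEs, the incidence of AEs, and correlation with the treatment". It gives no denominator or grouping of its own, so the ITT rule governs them. Grouping by assigned arm is not spelled out, but that is what the ITT principle means.

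On exposure, section 5 says "All participants received either acupuncture or ATs 3 times per week over the 8-week period". Section 7 provides for recording participants who leave the study, their reasons, and everyone's compliance.

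**The concern.** ITT suits efficacy because it preserves the randomised comparison, and the dilution that it allows usually works against claiming a benefit. For harm, dilution works the other way: it tends to make a treatment look safer, or two treatments look more alike. AE incidence and relatedness are questions about what a participant was exposed to. Someone who had no needling and no drops tells us nothing about the harm of either, yet counts in the denominator. A needling event in a participant assigned to artificial tears would be tabulated under tears.

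The situation could arise here. No masking of participants is described, and needling and eye drops are plainly distinguishable. Under section 5 the allocation is revealed after consent and before treatment, so a participant may decline on learning the arm. Treatment runs for 8 weeks and follow-up for another 24, and the documents state no restriction on obtaining the other treatment during that time.

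At stake is the accuracy of the reported AE rates and of the safety contrast between arms. The efficacy analysis is not affected.

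**Working it through.** The documents give no AE rate, non-starter count or crossover count, so there is no planned figure to reproduce. What follows shows the possible size under stated assumptions.

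**Inputs**
- Number randomised: section 5 says "the final group assignments were placed in 120 opaque sealed envelopes".
- Allocation: section 2 says "randomized into two groups—acupuncture and medicine—at a ratio of 1:1". Hence about 120 / 2 = 60 per arm. This is an assumption drawn from the envelope count.
- Assumed: *k* participants in an arm never start, the AE rate is *p* in treated participants and *q* in non-starters, and *c* participants receive the other treatment instead of their own.

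**1. Non-starters**

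ITT rate = [(60 − k)p + kq] / 60. The relative understatement is (k/60)(1 − q/p).

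With q = 0 (no AEs recorded in non-starters) this reaches its upper limit, k/60:

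| k | Relative understatement | An assumed true 10% is reported as |
|---|---|---|
| 0 | 0 | 10.0% |
| 2 | 2/60 = 3.3% | 10% × 58/60 = 9.7% |
| 5 | 5/60 = 8.3% | 10% × 55/60 = 9.2% |

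If non-starters who are still followed report unrelated AEs, the understatement is smaller. With q = p/2 and k = 5 it is 8.3% × 0.5 = 4.2%.

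**2. Zero events observed**

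The one-sided 95% upper bound is 1 − 0.05^(1/n):
- n = 60 (all randomised): 4.87%
- n = 58 (two non-starters removed): 5.03%
- n = 55 (five removed): 5.30%

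**3. Crossover**

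Assume AE rates of 10% on acupuncture and 2% on artificial tears, a true difference of 8.0 points.
- One direction only: difference = 8.0 × (1 − c/60). For c = 3 it is 7.6 points; for c = 6 it is 7.2.
- The same number in each direction: difference = 8.0 × (1 − 2c/60). For c = 3 it is 7.2 points; for c = 6 it is 6.4.

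The direction for a single arm depends on who moves:
- Three participants moving from acupuncture to tears lower the acupuncture arm's rate to (57 × 10% + 3 × 2%) / 60 = 9.6%.
- Three moving from tears to acupuncture raise the tears arm's rate to (57 × 2% + 3 × 10%) / 60 = 2.4%.

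In both cases the contrast narrows.

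**4. Does another part of the plan repair this?**

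The per-protocol set may remove non-starters and switchers, if those count as major deviations. It does not regroup anyone by treatment received, and it may also drop exposed participants whose events belong in a safety table. Section 9 requires participants with serious AEs to stop the intervention. With major deviation undefined, it is unclear whether they would stay in that set. A relatedness column flags individual events but corrects neither the denominator nor the arm.

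**The case against.** The strongest reply is that the documents show nobody untreated and nobody switching. Section 5 describes every participant as receiving one of the two treatments. Recording of early departures and compliance does not imply non-starters: a participant who begins and then stops belongs in both the ITT set and a safety set. The per-protocol analyses are not limited to efficacy and might exclude the affected participants. No safety threshold or formal safety hypothesis is stated that a shift of this size would overturn.

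Much of this stands. The effect is conditional and probably small. The section 5 sentence, however, describes the intended schedule and does not guarantee exposure, and the per-protocol set is no substitute for a safety set.

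A reader might infer more than the documents support:
- **That ITT lowers the AE rate in both arms.** Only non-starting does so directly, and k/60 is the full bias only if non-starters have no recorded AEs. Section 9 tabulates AEs as well as adverse reactions, so unrelated events may count. Crossover can raise an arm's rate.
- **That the plan contradicts itself by promising "the incidence of AEs, and correlation with the treatment".** Relatedness is judged event by event and can be recorded under any denominator. That text also stands two paragraphs after the ITT sentence.
- **That the distortion could be large.** Ten non-starters in 60 would give 17%, but nothing in the documents points to such a number.

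**Conclusion.** The point holds as a conditional defect in a stated rule. Section 9 names safety explicitly when it applies ITT, and no other section replaces that with a set based on exposure. If some participants never start, AE incidence is understated by up to k/60 in relative terms, about 3% for two and 8% for five. If some receive the other treatment, their events are credited to the wrong arm and the contrast tends to shrink. These sizes assume 60 per arm; the non-starter figures also assume no AEs recorded in non-starters, and the crossover figures rest on assumed AE rates of 10% and 2%. If everyone is treated as assigned, the planned tables and exposure-based tables are identical. It would go too far to say that the planned AE figures will be wrong, since the documents do not establish that anyone will be untreated or switched. This is a minor improvement that is worth making because it costs almost nothing.

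**What to change.** Keep ITT for efficacy. In section 9, define a safety set of all participants who received at least one acupuncture session or one use of artificial tears, group them by the treatment actually received, and use this set for every AE table. State in advance how participants exposed to both are handled, for example by attributing each event to the treatment received before its onset, or by listing them separately. Report the number randomised but never treated in each arm, so that the two denominators can be reconciled.

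The cost is one or two SAP sentences. Compliance is already recorded under section 7, so a treated denominator should be available. The sponsor should confirm that the case report form also captures use of the other treatment and event onset dates, which the documents do not state. The one downside is that reported AE rates may be slightly less favourable.

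### Randomisation is stratified by centre but no between-group analysis uses centre; the planned tests are on average conservative if the two hospitals differ in mean outcome

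*Combined protocol and SAP*

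**What the plan says.** Section 1 states the setting: "This is a two-center, prospective, controlled, randomized trial conducted in patients with moderate to severe DED". Section 2 sets 1:1 allocation between the arms. Section 5 describes the method: "Patients were randomly assigned to the acupuncture or AT group using a block size of 4 stratified by centers".

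Section 9 gives the between-group analyses. For continuous outcomes: "For comparisons of the differences between the two groups, T-tests or Mann–Whitney U tests will be used for comparisons between continuous variables". For categorical outcomes it names chi-square or Fisher's exact tests. It also lists within-group comparisons with baseline and a per-protocol sensitivity analysis. None of these has a centre term or a centre stratum, and no other section describes an analysis by centre.

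**The concern.** Blocks of 4 within each hospital keep the two arms nearly equal in size at each site. A difference in mean outcome between the hospitals then falls almost equally on both arms and drops out of the treatment difference. A two-sample t-test does not know this. It estimates its error from the total variance, which still contains the between-centre part, so the reported standard error exceeds the true one. The rank and contingency-table tests ignore the strata in the same way.

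What is at stake is efficiency and honest intervals. Stratification still reduces the true variance of the estimate, but the reported standard error, interval and p-value do not show it. The documents contain no sample-size or power calculation, so there is no stated margin to set against the lost efficiency.

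**Working it through.** **No plan figure to reproduce.** The documents state no effect size, SD or power. The check is of direction and size over an assumed range.

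**Inputs from the documents**
- Two centres (section 1); strata by centre, blocks of 4 (section 5); 1:1 allocation (section 2).
- N = 120, so 60 per arm. This is inferred from "the final group assignments were placed in 120 opaque sealed envelopes" (section 5).
- Two-sided tests at 0.05 (section 9), critical value 1.96.

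**Assumed inputs**
- R² = share of outcome variance due to centre: 1, 5, 10, 20%.
- Effect of 0.5 total SD, for the power figures only.

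**Formulas** (normal approximation, arms balanced within centre)
- Centre difference for equal-sized centres, in within-centre SDs: d = 2√(R²/(1 − R²)).
- Variance that the t-test assumes: V = 2/60 in units of total variance, so SE = 0.1826. True variance: (1 − R²)V.
- SE inflation: 1/√(1 − R²) − 1.
- Actual type I error: 2[1 − Φ(1.96/√(1 − R²))].
- Power, unadjusted: Φ((0.5/0.1826 − 1.96)/√(1 − R²)), where 0.5/0.1826 = 2.739.
- Power, adjusted for centre: Φ(2.739/√(1 − R²) − 1.96).

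Worked example at R² = 10%: √0.9 = 0.9487. Inflation is 1/0.9487 − 1 = 5.4%. Type I error is 2[1 − Φ(2.066)] = 3.9%. Unadjusted power is Φ(0.779/0.9487) = Φ(0.821) = 79.4%. Adjusted power is Φ(2.887 − 1.96) = Φ(0.927) = 82.3%.

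| R² | d | SE inflation | Type I error | Power, planned | Power, adjusted | Gain (points) |
|---|---|---|---|---|---|---|
| 0% | 0 | 0% | 5.0% | 78.2% | 78.2% | 0 |
| 1% | 0.20 | 0.5% | 4.9% | 78.3% | 78.6% | 0.3 |
| 5% | 0.46 | 2.6% | 4.4% | 78.8% | 80.2% | 1.4 |
| 10% | 0.67 | 5.4% | 3.9% | 79.4% | 82.3% | 2.9 |
| 20% | 1.00 | 11.8% | 2.8% | 80.8% | 86.5% | 5.7 |

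**Simulation check** (N = 120, blocks of 4 in two equal centres, no treatment effect; 8,000 trials per setting, 4,000 for Mann–Whitney)

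| d | t-test | Linear model with centre | Mann–Whitney | Mean t-test SE | True SD of estimate |
|---|---|---|---|---|---|
| 0.5 | 4.35% | 4.89% | 3.85% | 0.1875 | 0.1816 |
| 1.0 | 2.76% | 4.85% | 2.93% | 0.2039 | 0.1817 |

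Across all null settings, including a 70:30 split between centres, the model with centre kept type I error between 4.7% and 5.1%. By formula, the 70:30 split makes the t-test's conservatism slightly milder: 4.4% at d = 0.5 and 3.1% at d = 1.0.

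**Other way to state power.** If the within-centre SD is held fixed and the effect is set to give 80% power with adjustment (0.511 SD), the planned t-test has 79.7% at d = 0.2, 78.3% at d = 0.5 and 72.9% at d = 1.0. The mechanism is the same; only the reference SD changes.

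**The case against.** The case for leaving the plan alone has several parts.

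- **The effect may be negligible.** The two sites are a hospital and its own South Area, with common eligibility criteria, one training course, monthly supervision and allocation-unaware assessors for the scales. This points to similarity without proving it. At a 0.2 SD difference the type I error is 4.9%. This stands, and the range above includes that end.
- **The effect holds only on average.** A reader might infer that p-values are too large whenever the hospitals differ in any respect. The documents and the arithmetic do not support that. Only a difference in mean outcome matters; differences in size, or in practitioners or case mix that do not shift the mean, have no such effect. In a single dataset the adjusted SE can even be the larger one: it was smaller in 55% of simulated trials at d = 0.2 and in 96% at d = 0.5 (equal centres).
- **Examiner differences may cancel.** TBUT and CFS readings could differ by examiner, but section 9 leaves open whether the compared quantity is change from baseline. If it is, a constant examiner offset disappears, and only a centre difference in mean change remains. This stands.
- **The power figures show a forgone gain.** With total SD fixed, the planned test is never below the 78.2% that it has without a centre effect. This is correct in that framing, and it is why the result is given as a gain from adjustment.
- **Separate envelope series per centre are not described.** If one series had served both sites, balance within centre would not be forced and the type I figures would not apply. But section 5 states stratification by centre outright, and that statement is taken at face value here.

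A reader might also infer that the analysis is invalid or could produce a false positive. It is not biased, and the error is in the conservative direction only. The within-group comparisons with baseline are not affected in this way.

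**Conclusion.** The point holds as a free improvement. Centre is a stratification factor and no between-group analysis uses it; the text settles that. The consequence is conditional: if the hospitals differ in mean outcome, or in mean change where change is analysed, the planned tests are on average conservative. The size runs from negligible (type I error 4.9% when centre explains 1% of variance) to material (2.8%, with 5.7 points of power forgone, at 20%). These figures rest on 120 patients inferred from the envelopes, balance within centre, an assumed 0.5 SD effect for power, and centre shares that the documents do not supply. The percentages in the first table are for the t-test. Simulation shows the same direction for Mann–Whitney at centre differences of 0.5 SD and above; the size was not calculated for the chi-square and Fisher tests.

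**What to change.** Amend section 9 so that every between-group comparison uses centre:

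- continuous outcomes: a linear model with treatment and centre as fixed effects;
- where Mann–Whitney is planned: the van Elteren (centre-stratified) test;
- where chi-square is planned: Cochran–Mantel–Haenszel stratified by centre;
- where Fisher's exact test is planned: an exact conditional test stratified by centre.

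The same section should say whether the analysed quantity is the outcome value or its change from baseline.

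The cost is SAP wording and, for the linear model, one degree of freedom. Centre is already known from randomisation, so no new data are needed. If the hospitals turn out not to differ, almost nothing is lost.
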